#### Analysis

Recovery College characteristics were investigated using descriptive analysis exploring RECOLLECT Fidelity Measure scores and numerical characteristics such as student numbers. Hierarchical cluster analysis was used to create a national Recovery College typology. Content analysis of any free text survey responses and collaborative data analysis [34] using framework analysis [38, 39] of interview transcripts will be employed to explore organisational characteristics and pandemic impact. To assess costs, the expenses associated with Recovery Colleges will be identified and quantified, including salaries of those employed by the Recovery College and by other organisations who release employees as sessional trainers, building and IT costs, curriculum development and delivery, and time spent by stakeholders such as service users, informal carers and mental health staff who attend as students [26]. Costs will then be apportioned to specific sectors as appropriate with input and feedback from stakeholders.

### Work package 2: Prospective pre-post study exploring Recovery College impact on student mental health outcomes

Work package 2 will address Objectives 3 (Student outcomes), 4 (Fidelity, mechanisms and outcomes) and 9 (change model).

#### Design and rationale

Work Package 2 will consist of a prospective pre-post study at 25 Recovery Colleges selected from the survey sample to provide the full range of Fidelity Measure item scores. The change model and input from LEAP informed the development of items to assess the mechanisms of action and the choice of outcome measures, i.e. the primary outcome of quality of life and secondary outcome measures covering intrapersonal changes and changes to the students’ life including changes in service use. In addition, we will use the generic health status measure, EQ-5D-5L [40] to allow comparison of the samples in Work Package 2 and Work Package 3, and hence assess generalisability of the intervention group in Work Package 3.

#### Sample

To address Objective 3 we have conservatively assumed a small but clinically significant within-person effect size of 0.2 [41]. With standard deviation (SD) of 5 based on the mean difference of total score of the primary outcome measure, the Manchester Short Assessment (MANSA) [42] between baseline and follow up at 12 months with 95% power and 5% significance, assuming an intra-class correlation coefficient (ICC) of 0.02 [43, 44], an individual autocorrelation of MANSA score over time of 0.5 [45] and within-cluster standard deviation (SD) of 5, we require a sample size of 500. With an estimate of 20% attrition rate by 12 months, we will recruit 625 participants, for an analysable sample of 500. We will recruit 625 newly registering students (25 per college) who currently use secondary mental health services. Exclusion criteria will be insufficient knowledge of English to complete the outcome measures.

#### Measures

The primary outcome is quality of life as measured by the MANSA [46]. This comprises 12 items rated using a seven-point Likert scale, with higher scores indicating higher quality of life. The MANSA has been shown to have good psychometric properties, including internal consistency and validity [42, 47]. Secondary outcomes comprise: empowerment in relation to mental health service use, measured by the Mental Health Confidence Scale [48]; personal recovery measured by Brief INSPIRE-O [49]; social inclusion measured by the Social Inclusion Scale/Measure (Social inclusion) [50]; resilience measured by the Brief Resilience Scale [51]; hope as measured by the Herth Hope Index [52]; Social network size using the Lubben Social Network Scale 6 [53]; and mental wellbeing, using the Warwick-Edinburgh Mental Wellbeing Scale (Short version) [54].

Student service use will be measured using a Service Use Questionnaire designed for the project and will capture both NHS and non-NHS service use. The SUQ covers contacts with health and social care, use of leisure facilities, employment, income and out of pocket expenses. We will include the number and types of RC courses attended. To provide a societal perspective, it will be tailored to cover work status and absence, sources of income, domestic activities, informal care, medication use, out-of-pocket expenses, and consumption of non-medical resources. Where consent is given by students, mental health clinical records will be accessed to supplement findings.

The EQ-5D-5L is a self-rated measure of health-related quality of life [40]. The scale measures quality of life on a 5-component scale including mobility, self-care, usual activities, pain/discomfort, and anxiety/depression. Psychometrically, it is less prone to ceiling effects than the EQ-5D-3L across a range of diseases [55, 56]. The National Institute for Health and Care Excellence (NICE) requires use of a 5L to 3L crosswalk algorithm for their reference-case to estimate QALYs [57].

#### Procedures

All new students will be made aware of the research by Recovery College staff as they register. Those who express interest in participating will be contacted by a member of the research team who will provide the participant information sheet either remotely or in person. Participation will be optional, and students can choose to register with the college and not take part in the RECOLLECT Study. Eligible students who provide informed consent will then complete baseline measures, sociodemographic data and provide follow-up contact information for re-administration of all measures at 4, 8, and 12 months. Clinical and service use data will be collected from electronic medical records given participant consent for access; this consent will be optional for those consenting to participate in measure completion.

#### Analysis

To address Objective 3 (Student outcomes), we will compare primary outcome (total MANSA score) at baseline, 4, 8, and 12 months follow-up adjusted for baseline total MANSA score and accounting for hierarchical clustering of students at the level of Recovery College. The model will include the MANSA score as the outcome variable, baseline MANSA score and socio-demographic characteristics as explanatory variables at each time point. Specifically, we will fit a three-level random intercept linear regression model, considering observations from baseline, 4, 8 and 12 months at level 1, individuals at level 2 and Recovery Colleges at level 3. Secondary outcomes will be assessed similarly to the primary outcomes, using generalized linear mixed models (logistic, linear and Poisson depending on the distribution of our outcome variable).

The relationship between Fidelity Measure scores at the Recovery College level with primary and secondary outcomes will also be assessed using generalised linear mixed models. Where significant associations emerge, theoretical mechanisms of action will be added to models to examine potential mediating effects.

If indicated, we will refine the RECOLLECT multilevel change model by removing outcomes where there is no evidence of change at any time point.

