#### Design and rationale

Work package 3 will employ a prospective controlled study design and include seven of the Recovery Colleges from Work Package 2, with which it will run in parallel. A non-randomised design will be employed due to the impossibility of individual level randomisation; most mental health service users have access to a Recovery College, even if not available in their Trust. The seven Recovery Colleges were selected for being linked to an NHS Trust which has access to a Clinical Record Interactive Search (CRIS) system, as this will be used to identify the control group.

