#### Analysis

We will compare the total MANSA score for service users who attended a Recovery College (intervention group) with those who did not (control group) at each follow up, controlling for baseline scores and hierarchical clustering of patients in Recovery Colleges. Specifically, we will fit a three-level random intercept linear regression model, considering observations from baseline, 4, 8 and 12 months at level 1, individuals at level 2 and Recovery Colleges at level 3. The model will include the MANSA scores at 4, 8 and 12 months as the outcome variables with intervention group, baseline MANSA score and sociodemographic characteristics, including the matching factors. A time x intervention interaction will be included to allow the effect to differ at each time point. Those secondary outcomes collected in both the intervention and control groups will be assessed similarly to the primary outcomes, using generalized linear mixed model (linear, logistic and Poisson depending on the distribution of the outcome.

Incremental economic analyses will be conducted from both a healthcare and a societal perspective with analyses conducted at 4, 8 and 12-month follow-up, controlling for baseline. Uncertainty will be addressed by generating cost-effectiveness planes from bootstrapped resamples. Cost effectiveness acceptability curves will examine the probability that the intervention is cost-effective for different decision-maker willingness-to-pay thresholds, as well as generating net benefit estimates. Sensitivity analysis will investigate key factors including the impact of costs of different Recovery College delivery models and the use of EQ-5D-5L/EQ-5D-3L cross-walk methods to generate utility [57]. The benefits of Recovery Colleges are likely to continue after the 12-month primary endpoint. Therefore, we will also carry out an economic evaluation informed by modelling to estimate longer-term benefits and NHS/Personal and Social Service and wider costs, using current design quality standards [59]. This requires an expert consensus panel to support model design, made up of Lived Experience Advisory Panel, Recovery College staff and the applicants, and representatives of Trusts and other affiliated organisations.

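### Work Package 2 uses baseline MANSA as both outcome and covariate, which biases the 12-month change if dropout depends on baseline; Work Package 3 contradicts itself on the same point

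*Protocol article*

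**What the plan says.** **Work Package 2, Analysis.** The comparison is introduced as: "we will compare primary outcome (total MANSA score) at baseline, 4, 8, and 12 months follow-up adjusted for baseline total MANSA score". The covariates follow: "The model will include the MANSA score as the outcome variable, baseline MANSA score and socio-demographic characteristics as explanatory variables at each time point". The hierarchy is then a three-level random-intercept model "considering observations from baseline, 4, 8 and 12 months at level 1, individuals at level 2 and Recovery Colleges at level 3". All three statements fit together, and together they enter baseline MANSA as an outcome row and as a predictor. Secondary outcomes are to be handled in a similar way.

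**Work Package 3, Analysis.** The hierarchy sentence is repeated: "considering observations from baseline, 4, 8 and 12 months at level 1". The next sentence says otherwise: "The model will include the MANSA scores at 4, 8 and 12 months as the outcome variables with intervention group, baseline MANSA score" and further covariates. It continues: "A time x intervention interaction will be included to allow the effect to differ at each time point". The Design and rationale section for this work package states that "A non-randomised design will be employed due to the impossibility of individual level randomisation".

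**The concern.** On a baseline row the outcome is the covariate, so the true slope is 1 and no residual variation is left. On a follow-up row the slope is the correlation over time, which the Work Package 2 sample size section sets at 0.5. One common slope fits neither kind of row, and the random intercept then describes a residual structure that the data do not have.

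Objective 3 is the change from baseline, and the planned effect is only 0.2 SD, so a modest distortion is a visible share of it. Work Package 2 also removes outcomes from the change model when no change is seen, so the same model form reaches the secondary outcomes and Objective 9.

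In Work Package 3 the two sentences cannot both be fitted. Without randomisation, the groups may differ on baseline MANSA, and that is when the choice between the two models matters.

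**Working it through.** **Inputs from the article (Work Package 2, Sample).** Effect 0.2, SD 5, autocorrelation 0.5, ICC 0.02, power 95%, significance 5%, attrition 20%, 25 colleges with 25 students each.

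**The plan's own figure.** The SD of a change is 5 × √(2 × (1 − 0.5)) = 5, so the effect is 0.2 × 5 = 1 point. Then n = (1.960 + 1.645)² / 0.2² = 325. The design effect 1 + 24 × 0.02 = 1.48 gives 481, and 20 analysable per college × 25 gives 500. Finally 500 / 0.8 = 625. The stated figures are reproduced, so these inputs are a fair basis for the check. The article gives no figure for the bias, so it was simulated.

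**Work Package 2.** Settings: SD 1, correlation 0.5 between visits, true 12-month change 0.20, 20% dropout, college level left out because it does not drive this bias. *Assumed:* the relation of dropout to baseline. The table has higher-scoring students dropping out.

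| Log-odds of dropout per SD | Baseline gap, completers v dropouts | Estimate, all follow-ups lost | Bias as share of 0.20 | Estimate, dropout spread over visits |
|---|---|---|---|---|
| 0.25 | 0.25 SD | 0.211 | about 5% | 0.209 |
| 0.5 | 0.48 SD | 0.222 | about 11% | 0.217 |
| 1 | 0.87 SD | 0.241 | about 20% | 0.231 |

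If lower-scoring students drop out, the sign reverses (0.16 at log-odds 1). If dropout is unrelated to baseline, the estimate is 0.198. The model without the baseline covariate gives 0.20 throughout.

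*Check by hand.* Let β be the fitted slope (about 0.66) and ρ the fitted residual correlation (about 0.2). Let the shift be the mean baseline of those still seen minus that of everyone, which is 0.2 × gap. Follow-up rows are over-adjusted by (β − 0.5), and the random intercept carries over part of the baseline-row residual (1 − β). The absolute bias is about [(0.66 − 0.5) + 0.2 × 0.34] × shift = 0.228 × shift:

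- gap 0.25: 0.228 × 0.050 = 0.011
- gap 0.48: 0.228 × 0.096 = 0.022
- gap 0.87: 0.228 × 0.174 = 0.040

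Divided by 0.20 these are 6%, 11% and 20%, in line with the table.

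*Coverage at n = 625*, dropout spread over visits: 92% and 89% at log-odds 0.5 and 1, against 95% and 96% without the covariate. At correlation 0.7 the bias is smaller: 0.95 and 0.90 of the true change, against 0.93 and 0.84 at correlation 0.5.

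**Work Package 3, only if baseline rows are kept.** True adjusted effect 1 point. *Assumed:* the intervention group starts 1 point (0.2 SD) higher.

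- Group × time term at 12 months: (1 + 0.5 × 1) − 1 = 0.50; simulated 0.51.
- Adjusted 12-month difference: 1 + 0.5 × 1 − 0.64 × 1 = 0.86; simulated 0.86.
- With the group 1 point lower: simulated 1.48 and 1.13.
- With no imbalance there is no bias. At n = 660, however, the model SE of the adjusted difference is 0.33 against an empirical 0.40, and coverage is 90%.

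**Work Package 3 with 4, 8 and 12 months only.** The effect is 0.99 to 1.03 in every scenario, with coverage of 94% to 95% at n = 660.

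**The case against.** Four points deserve weight.

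1. **Dropout alone does no harm.** A reader might infer that 20% attrition by itself biases the change. It does not: dropout must be related to baseline MANSA, and the article states no such relation. This stands, so the sizes are conditional.
2. **The 20% is the strongest scenario.** It needs completers and dropouts to be 0.87 SD apart at baseline. Milder relations give 5% to 11%. In runs at n = 625 without college clustering, power stayed above 99%, so detection of a change is not threatened. This stands too, and it lowers the severity.
3. **Another reading is possible.** Describing the covariates as explanatory at each time point could mean a separate baseline slope per visit. With centred baseline × time terms the estimate is 0.199 to 0.200 in every dropout scenario, with coverage of 93% to 94% at n = 625. But the article states no such interaction for Work Package 2, and even then the baseline rows are redundant.
4. **Work Package 3 is not shown to be biased.** A reader might infer that its group effect is wrong as planned. The article does not support that: its explicit list of outcomes, "The model will include the MANSA scores at 4, 8 and 12 months as the outcome variables", with baseline as covariate, is the correct model. Dropout similar in both groups also causes no bias there. What remains is the contradiction between two adjacent sentences.

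It could also be said that an article condenses and a full analysis plan may settle this. But here the model is not left out; it is stated, and in Work Package 2 stated wrongly.

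**Conclusion.** The point holds, as a should-fix. Work Package 2 specifies baseline MANSA as outcome and covariate in its primary model. With a common baseline slope, the 12-month change is off by roughly 5% to 20% of the assumed 0.2 SD effect when dropout has log-odds of 0.25 to 1 per SD of baseline. The direction depends on who drops out, and there is no bias when dropout is unrelated to baseline. These figures rest on the article's correlation of 0.5 and attrition of 20%, and on an assumed dropout relation.

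Work Package 3 has an internal contradiction to reconcile. One of its two sentences gives a sound model. The other would distort the group effect under baseline imbalance, by about half the imbalance in the group × time term and about 0.14 of it in the adjusted difference, measured against the baseline-adjusted effect. It would also understate the standard error of the adjusted difference. The size of any imbalance is not given in the article.

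**What to change.** - **Work Package 2:** keep all four visits as outcomes, enter time as a categorical fixed effect, drop the baseline MANSA covariate (the sociodemographic covariates can stay), and report the 12-month minus baseline contrast.
- **Work Package 3:** delete baseline from the level-1 sentence, so that the outcomes are 4, 8 and 12 months with baseline MANSA as a covariate.
- **Secondary outcomes:** apply the same rule in each work package.

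This costs analysis wording only. No data collection, sample size or participant burden changes. Nothing is lost in Work Package 2, because the baseline score still enters as an outcome visit.

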#### Procedures

Work Package 3 will run alongside Work Package 2. At the seven Recovery College sites involved in Work Package 3, participants will be asked if they would like to take part in Work Package 3 by consenting to data linkage using CRIS. Those that consent will comprise the intervention group for Work Package 3. This is outlined in Fig. 4 below. To identify the control group, propensity score matching [58] will be employed using the CRIS system at each site. This is a statistical matching technique that attempts to create a comparable control group for the Recovery College intervention group by accounting for the covariates, such as demographics and clinical history, that predict outcomes. Reverse anonymisation will be undertaken by CRIS staff and potential control participants will be contacted by NHS Trust staff working with CRIS staff to find out if participants are interested in hearing more about the study. Those that are will be provided with information sheets and will need to give informed consent to take part. The intervention group will complete those measures used in Work Package 2 and listed above at the same time points of baseline, 4, 8 and 12 months. The control group will complete the primary outcome measure and a restricted set of those measures used in Work Package 2 and the Work Package 3 intervention group, to reduce burden. Participants in Work Packages 2 and 3 will be compensated for their time completing assessments.

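### WP2: a college random intercept alone cancels from the change since baseline, so the analysis does not make the clustering allowance that the sample size of 500 appears to contain

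*Protocol article*

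**What the plan says.** Work Package 2, Analysis: the primary analysis follows total MANSA over time. The text says "we will compare primary outcome (total MANSA score) at baseline, 4, 8, and 12 months follow-up adjusted for baseline total MANSA score", and then "Specifically, we will fit a three-level random intercept linear regression model", with the scores at baseline and at all three follow-ups placed at level 1, individuals at level 2 and Recovery Colleges at level 3. Baseline MANSA also appears among the explanatory variables. No college-by-time effect or other random effect beyond the intercepts is named.

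Work Package 2, Sample: the calculation concerns the change in MANSA from baseline to 12 months. It uses an effect size of 0.2, SD 5, 95% power, 5% significance and an individual autocorrelation of 0.5, "assuming an intra-class correlation coefficient (ICC) of 0.02". The result is 500 analysable participants, or 625 recruited to allow for 20% attrition, at 25 colleges.

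Work Package 3, Analysis: the same three-level structure is used, "controlling for baseline scores and hierarchical clustering of patients in Recovery Colleges". Here the outcomes are named as the scores at 4, 8 and 12 months, with baseline as a covariate. "A time x intervention interaction will be included to allow the effect to differ at each time point". On controls, the Procedures section says "propensity score matching [58] will be employed using the CRIS system at each site". The article does not say which level-3 unit a control belongs to.

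**The concern.** A random intercept for college describes differences in level between colleges. When baseline is one of the level-1 outcomes, the quantity of interest is a difference between two occasions in the same people at the same college, and the college intercept is subtracted out. The model then treats the true change as identical in all 25 colleges. If change does differ between colleges, that variation is pooled into the residual as though it were independent between students, and the standard error of the mean change is too small for inference to Recovery Colleges in general.

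Two features of the plan suggest that its authors expected such variation. The sample size carries an allowance for clustering, and the 25 colleges are chosen to span the fidelity range so that fidelity can be related to outcomes. At stake are the confidence interval and p-value for Objective 3. The same approach is used for the secondary outcomes, and outcomes without evidence of change may be removed from the change model, so false-positive change would keep outcomes in it.

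**Working it through.** **Inputs from the article (Work Package 2, Design and rationale, and Sample).** Effect size 0.2; SD 5; 95% power; 5% significance (two-sided assumed); ICC 0.02; individual autocorrelation 0.5; 25 colleges; 500 analysable, so m = 500/25 = 20 per college.

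**Step 1: SD of the change.** Variance of change = 2 × 25 × (1 − 0.5) = 25, so the SD is 5, as stated.

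**Step 2: reproduce the 500.**
- No clustering, normal quantiles: (1.960 + 1.645)² / 0.2² = 325.
- No clustering, t quantiles on 24 df (25 colleges): (2.064 + 1.711)² / 0.2² = 356.
- Design effect on change with ICC 0.02: 1 + (20 − 1) × 0.02 = 1.38.
- 325 × 1.38 = 448; 356 × 1.38 = 492. The second is within 2% of 500, and power at 500 on that basis is 95.5%.
- With 25 per college and normal quantiles: 325 × (1 + 24 × 0.02) = 325 × 1.48 = 481.
- Attrition: 500 / 0.8 = 625, as stated.

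**Step 3: what the stated model would have needed.** If the college effect is purely a stable intercept, it leaves the change altogether. The design effect is then 1 − 0.02 = 0.98, and n = 325 × 0.98 = 318 (normal) or 356 × 0.98 = 349 (t, 24 df). The figure of 500 is therefore not explained by the random-intercept model. It is approached only if change itself is clustered.

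**Step 4: consequence for the standard error.** The random-intercept model gives SE = 5/√500 = 0.224. If the ICC of change is ρ, the true SE is 0.224 × √(1 + 19ρ), and the actual error rate of the nominal 5% test is 2 × [1 − Φ(1.96/√(1 + 19ρ))].

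| ICC of change (assumed) | Design effect | True SE | Actual error rate |
|---|---|---|---|
| 0 | 1.00 | 0.224 | 5.0% |
| 0.01 | 1.19 | 0.244 | 7.2% |
| 0.02 | 1.38 | 0.263 | 9.5% |
| 0.05 | 1.95 | 0.312 | 16% |

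At 0.02 the modelled SE is 0.224/0.263 = 0.85 of the true one, that is, 15% too small. Simulations at 0.02 gave 9.3% and 9.9%. A t-test on college-level changes stayed close to 5%.

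**Step 5: how 0.02 could refer to change.** If the ICC describes scores at one occasion, the college variance is 0.02 × 25 = 0.5, and the college variance of change is 2 × 0.5 × (1 − c), where c is the correlation of a college's effect over time. With c = 0.5 this is 0.5, or 0.5/25 = 0.02 of the variance of change. With c = 1 it is zero, and the error rate is 5%. The article gives no value for c.

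**Step 6: the other reading of baseline.** If only follow-up scores are outcomes and baseline is a covariate, the college intercept belongs to baseline-adjusted follow-up and does not cancel. Simulation at ICC 0.02 then gave a mean SE of 0.246 against a true 0.260, and an error rate of 6.8%. That rate does not rise with the ICC (7.9% at 0, 7.0% at 0.05), so the remaining excess does not come from unmodelled variation between colleges.

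**The case against.** The strongest reply is that the Work Package 2 text gives baseline two roles. It is a level-1 observation, but also something adjusted for. Work Package 3 uses the same level-1 sentence and yet names only the follow-up scores as outcomes. Read that way, the Work Package 2 intercept does not cancel and most of the problem goes. This stands as a limit on the size of the point, but not as an answer to it. The sentence that specifies the model puts baseline at level 1, and one model cannot sensibly use baseline both ways.

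Second, the harm depends on an unstated quantity. The article does not say that its ICC applies to change, and how its authors reached 500 is inferred from a calculation that gives 492. With no variation in change the test holds 5%. This stands too, and the size has to be given as a range. A related reply is that the colleges were chosen purposively, so a common-change model could be defended for the average over these 25. The aims, however, concern Recovery Colleges in England, which favours the wider target.

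Third, Work Package 3. A reader might infer that its group effect suffers in the same way, because controls are matched within sites and a shared intercept would cancel from student minus control. The document does not support stating this as fact. Controls attend no college, their level-3 unit is not given, and if the college effect applied to students only it would not cancel. No site-by-group variance is given either. Error rates of 6% to 19% follow only from assuming a between-site SD of effect of 0.05 to 0.20 SD (330 per group, baseline correlation 0.5).

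**Conclusion.** The point holds for Work Package 2 in conditional form. As written, with baseline at level 1 and random intercepts only, the model makes no allowance for change differing between colleges, although the stated sample size is approached only with a design effect of about 1.38 on change. If the ICC of change is 0.02, the SE is about 15% too small and the nominal 5% test runs at about 9.5% to 10%. The figure is 5% with no variation, about 7% at an ICC of 0.01, and about 7% if baseline serves only as a covariate. A flat statement that the standard errors are too small would go further than the article allows.

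For Work Package 3 what remains is a gap in definition: the level-3 unit for controls. An understated standard error there is possible but not shown.

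**What to change.** **Work Package 2.** Add a college-by-time random effect, or analyse mean change per college, with small-sample degrees of freedom for 25 colleges (Satterthwaite or Kenward-Roger in the mixed model; 24 df for college means). State whether baseline MANSA is an outcome or a covariate, and use it in that role only.

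This changes analysis wording and needs no new data. The cost is a somewhat wider interval. If the ICC of change is 0.02, the half-width goes from 1.96 × 0.224 = 0.44 to 2.064 × 0.263 = 0.54 MANSA points, against a target change of 0.2 × 5 = 1 point. Power at 500 stays at about 95.5%, because the sample size already covers this design effect.

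**Work Package 3.** State that level 3 for controls is the site at which they were matched, and report site-by-intervention variation as a sensitivity analysis. It should not become the primary model. Seven sites estimate that variance poorly, the document gives no value for it, and with 6 df power would be about 58% (assuming 330 per group, a between-site SD of effect of 0.10 SD and a baseline correlation of 0.5).

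### The random-intercept-only MANSA models assume the same variance and correlation at every visit; if within-person correlation fades, the 12-month standard error is too small and the 4-month one too large

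*Protocol article*

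**What the plan says.** The Analysis sections of Work packages 2 and 3 in the protocol article fix the same form of model for total MANSA score: "we will fit a three-level random intercept linear regression model, considering observations from baseline, 4, 8 and 12 months at level 1", with individuals at level 2 and Recovery Colleges at level 3. Neither section mentions a random slope, a residual covariance structure, visit-specific variances or robust standard errors.

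Work Package 3 adds: "The model will include the MANSA scores at 4, 8 and 12 months as the outcome variables with intervention group, baseline MANSA score", and "A time x intervention interaction will be included to allow the effect to differ at each time point". That interaction frees the means at each visit and leaves the covariance as it was.

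The Sample section of Work package 2 plans on change from baseline to 12 months, with "an individual autocorrelation of MANSA score over time of 0.5" and "assuming an intra-class correlation coefficient (ICC) of 0.02". No lag-specific correlations are given. The economic paragraph of the Work package 3 Analysis section refers to 12 months as the main time point: "The benefits of Recovery Colleges are likely to continue after the 12-month primary endpoint".

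**The concern.** A single random intercept per person, with the usual independent residuals, treats two scores 4 months apart as no more alike than two scores 12 months apart. It also estimates one residual variance from all lags together. Repeated self-report scores often correlate more strongly when taken closer together. If that happens here, the pooled variance is too small for comparisons spanning 12 months and too large for those spanning 4.

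The 12-month intervals would then be too narrow and the nominal 5% error rate exceeded, while the 4-month tests would be conservative. Both directions matter. Both Work Packages compare at every follow-up, and Work Package 2 intends to drop outcomes from the change model when no time point shows change.

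**Working it through.** **Inputs from the article.** Work Package 2: SD 5, effect size 0.2 (so a change of 0.2 × 5 = 1 point), correlation 0.5, ICC 0.02, 95% power, 5% significance, 25 colleges, 500 analysable. Work Package 3: 330 per group.

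**The plan's own figure.** n = (1.960 + 1.645)² × 2 × 5² × (1 − 0.5) / 1² = 325 before clustering. With 20 per college the design effect is 1 + 19 × 0.02 = 1.38, giving 448. With 25 per college it is 1.48, giving 481, which is 500 after rounding up to 20 per college. Using t quantiles on 24 degrees of freedom with 20 per college gives 492. Then 500 / 0.8 = 625. So 500 is closely reproduced, with 0.5 acting as the baseline-to-12-month correlation.

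**Assumed patterns.** The 12-month correlation stays at 0.5 and the variance is equal at all visits. Correlations at lags of 4/8/12 months are:
- constant: 0.50/0.50/0.50
- A: 0.60/0.55/0.50
- B: 0.70/0.60/0.50
- C, first-order decay: 0.79/0.63/0.50

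**Work Package 2, baseline as an outcome occasion.** Four visits give three pairs 4 months apart, two pairs 8 months apart and one pair 12 months apart. With balanced data the model takes the variance of any change as proportional to 2(1 − r̄), where r̄ = (3r₄ + 2r₈ + r₁₂)/6. The true variance is proportional to 2(1 − r) at the lag concerned. The ratio of model to true SE is √[(1 − r̄)/(1 − r)], and type I error is 2[1 − Φ(1.96 × ratio)]. The college intercept cancels from within-person change.

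| Pattern | r̄ | 12-month SE ratio | Type I error | 4-month SE ratio |
|---|---|---|---|---|
| Constant | 0.500 | 1.000 | 5.0% | 1.000 |
| A | 0.567 | 0.931 | 6.8% | 1.04 |
| B | 0.633 | 0.856 | 9.3% | 1.11 |
| C | 0.690 | 0.787 | about 12% | 1.23 |

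Example, pattern B: r̄ = (2.10 + 1.20 + 0.50)/6 = 0.633. At 12 months, √(0.367/0.500) = 0.856. At 4 months, √(0.367/0.300) = 1.11.

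**Work Package 3, baseline as covariate.** With one baseline slope b = (r₄ + r₈ + r₁₂)/3, the residual variance at a visit is 1 − 2br + b². The model uses the mean of the three.

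| Pattern | b | Residual variance at 4, 8, 12 months | 12-month SE ratio | Type I error | 4-month SE ratio |
|---|---|---|---|---|---|
| A | 0.55 | 0.64, 0.70, 0.75 | 0.963 | about 6% | 1.04 |
| B | 0.60 | 0.52, 0.64, 0.76 | 0.918 | about 7% | 1.11 |
| C | 0.64 | 0.39, 0.60, 0.77 | 0.875 | about 9% | 1.22 |

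If baseline is only a covariate in Work Package 2, these smaller figures apply there too.

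**Simulation check** (2,000 datasets per case; Work Package 2 with 500 people in 25 colleges, Work Package 3 with 330 per group in seven sites). Work Package 2 type I error was 5.3% under constant 0.5, 10.0% under B and 12.0% under C. Work Package 3 gave 5.4%, 7.0% and 9.6%. Under C, the actual against the model SE at 12 months was 0.225 against 0.176 in Work Package 2 and 0.347 against 0.299 in Work Package 3. College was handled simply: site terms in Work Package 3, and a person intercept only in Work Package 2.

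**Unequal variance alone.** With constant correlation 0.5, letting the SD rise in equal steps from 1 to 1.15 makes the Work Package 3 12-month SE about 4% too small. Letting it fall to 0.85 makes it about 6% too large. There is no fixed direction.

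**The case against.** The strongest reply is that nothing goes wrong under the plan's own inputs. The article gives one correlation, a random-intercept model matches one correlation, and type I error is then 5%. Every inflated figure comes from a lag pattern that the article does not state. This stands, and it makes the point conditional. The 12% figure is the far end: pure first-order decay leaves no room for measurement error in a self-report scale.

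A second reply is that residual structure belongs in the analysis plan, which is not shown and could free the covariance or use robust standard errors. That is possible. But the article goes beyond a generic mixed model and specifies random intercepts for the primary analysis, so an analysis plan that follows it carries the restriction forward.

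Third, a reader might infer that standard errors are too small throughout. They are not: those at 4 months err the other way.

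Fourth, a reader might infer that both Work Packages are sized on 12 months. The Work Package 3 sample-size statement names no time point; only the economic paragraph calls 12 months the primary endpoint.

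Fifth, a reader might infer that the expected 20% attrition is handled worse as a result. The article states no missing-data method and no calculation here bears on it, so that is not claimed.

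**Conclusion.** The point holds as a conditional weakness in a stated primary model, and as a cheap improvement. It does not show that the planned analysis will be in error. If within-person correlation fades while the 12-month value stays at 0.5, the random-intercept model understates the 12-month SE by about 7% to 21% for Work Package 2 change with baseline as an outcome occasion. The understatement is about 4% to 12.5% for the Work Package 3 contrast, or for Work Package 2 with baseline only as a covariate. Type I error is then about 7% to 12% and about 6% to 9% respectively. The 4-month SEs are overstated by about 4% to just over 22%. If correlation is constant, none of this arises.

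The figures assume complete data, equal variances, model-based standard errors with independent residuals, and baseline used in one role only. The effect is modest in Work Package 3, the controlled comparison; the larger figures concern an uncontrolled pre-post change.

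**What to change.** For the linear MANSA models, keep the college random intercept and replace the person-level intercept with an unstructured within-person covariance across visits.

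- **Work Package 3:** a 3×3 matrix over 4, 8 and 12 months, with baseline MANSA as covariate and a baseline-by-time term.
- **Work Package 2:** either a 4×4 matrix with baseline as an outcome occasion and removed from the covariates, or a 3×3 matrix with baseline as covariate only. The Analysis section currently gives baseline both roles. With a free variance per visit that would fail, because the covariate fits the baseline occasion exactly and its residual variance collapses to zero.
- **Fallback:** name one in advance for non-convergence, such as heterogeneous first-order autoregressive.

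The cost is a few covariance parameters (6 for 3×3, 10 for 4×4) with 500 or more participants, and some risk of non-convergence. No new data are needed, and the Work Package 2 sample size is unchanged if 0.5 is the 12-month correlation. If correlation turns out constant, almost nothing is lost. The change does not carry over to logistic or Poisson secondary models, which need their own specification.
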